**Secondary measures**	
-Illness duration	Days from the initial consultation to the day when the patient has reported full recovery based on the patient’s responses to question item A3a in Additional file 1, item B1b in Additional file 2, and item C1b in Additional file 3.
-Illness severity	Ten-point Likert rating of symptom severity based on the patient’s responses to question item A3b in Additional file 1, item B1c in Additional file 2, and item C1c in Additional file 3.
-Times of re-visits	Times of re-visits to the same clinic as the initial consultation + visits to other clinics for the same RTI episode based on the patient’s responses to question items C3a1, C4b12, and C4b22 in Additional file 3.
-Antibiotics re-prescription	Times of antibiotics re-prescription during the patient’s re-visits to the same clinic as the initial consultation and visits to other clinics for the same RTI episode based on the patient’s responses to question items C3a2, C3a3, C3a4, C4a3, C4b15, and C4b25 in Additional file 3.
-Knowledge about and attitude toward antibiotics	Percentage of correct responses to the questions relating to knowledge and attitude about antibiotics, i.e., item D1 in Additional file 4.
-Times of re-occurrence of RTIs	Times of re-occurring RTI episodes 180 days or 365 days following the initial consultation based on the patient’s responses to question item D2a1 in Additional file 4.
-Health service seeking for re-occurred infections	Times of visits to clinics for re-occurring RTI episodes 180 days or 365 days following the initial consultation based on the patient’s responses to question item D2b1-D3c41 in Additional file 4.
-Antibiotics consumption for re-occurred infections	Times of antibiotics prescriptions for re-occurring RTI episodes 180 days or 365 days following the initial consultation based on the patient’s responses to question items D2b3, D2c3, and D3c3 in Additional file 4.
-Quality of life (EQ-5D-5L)	Quality-adjusted life years based on the patient’s responses to the EQ-5D-5L scales in Additional file 5.
-Attitude toward intervention messages	Percentage of ideal responses to the questions relating to attitude toward the intervention messages, i.e., item B3d-B3e in Additional file 2, item C5d-C5e in Additional file 3.
-Understanding of intervention messages	Percentage of ideal responses to the questions relating to the understanding of the intervention messages, i.e., item B3c in Additional file 2, item C5c in Additional file 3.

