Day 9	Dear [PatientName], your current illness suggests that every on including you can get respiratory tract infections. Therefore, you need to strengthen your personal protection in the future. This include: eat more fresh vegetables and fruits; exercise more; wash hands more frequently; avoid crowded places when many people around you are having respiratory symptoms and wear a mask when you go out. From [DoctorName] with [ClinicName].
Day 10	Dear [PatientName], a certain proportion of respiratory tract infections are influenza. Influenza is highly contagious and easy to increase the extra risk of common health conditions like chronic respiratory tract diseases and cardiovascular and cerebrovascular diseases. Therefore, the State encourages residents to get influenza vaccination, especially for the elderly over 60 years old, patients with chronic diseases, children aged 6 months to 5 years and caregivers for infants under 6 months. From [DoctorName] with [ClinicName].
Day 11	Dear [PatientName], after recovery from your current illness, if you have respiratory symptoms next time in the future, please do not hurry seeing a doctor but wait and watch its progression, do not go to retail medicine shop to buy antibiotics without a prescription, and do not take leftover antibiotics. Please practice rest at home, drink more water and eat more protein-rich and digestible food and more fresh vegetables. Most respiratory infections are self-limiting and the symptoms start to relief within a few days. From [DoctorName] with [ClinicName].
Day 12	Dear [PatientName], this is the last message we plan to send you. We hope you will do as what the messages have suggested and avoid antibiotics use whenever possible. Antibiotics have no effect on most respiratory infections - they cannot relief the severity of symptoms or shorten the disease duration. On the contrary, antibiotics are easy to cause drug resistance and various other side effects. Thank you for accepting and reading all the messages and all the best wishes for you. From [DoctorName] with [ClinicName].

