#### Message tailoring

The study uses a novel computerized method in tailoring the messages to the need and context of individual patients. More specifically, each of the messages is designed as a template inserted with substitution variables to be replaced with relevant values and/or text according to the actual conditions and contexts of the patient under concern. Taking the example of the message to be sent on day 1 (Table 1), it contains seven variables specified as “[PatientName],” “DiseaseDiagnosis,” etc. When sent to a patient, for example, named “Li Si,” who has consulted doctor Zhang San at “SanXiaoKou Community Health Center” for sneezing, stuffy nose, and sore throat and the doctor diagnosed the illness as “common cold.” The message is changed to: “Dear Li Si, many thanks for your trust and visit to our clinic for a common cold. What you were experiencing were mainly sneezing, stuffy nose and sore throat. These are very common symptoms. They generally reach a peak within 1-3 days and then begin to relieve gradually. You needn’t see any doctor again unless you do not get better within 14 days. From [name] with SanXiaoKou Community Health Centre.”

Most of the substitution variables are determined by built-in computerized algorithms based on literature reviews or findings from the research team’s previous investigations and the expert consensus mentioned earlier. Taking the example of the “normal duration,” the online system has a built-in “dictionary” which reads like {“diagnose 1”: duration 1, “diagnose 2”: duration 2, …, “diagnose *n*”: duration *n*}. So, the online system can automatically provide a relevant duration value upon the diagnose entered by the doctor.

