#### Data collection

The study data will be collected through one baseline and five follow-up telephone interviews. For any recruited patient, the baseline interview happens immediately after the consultation, while the follow-up interviews are scheduled at 7, 14, 21,180, and 365 days after the baseline. The interviews will be performed by trained data collectors using a structured questionnaire adapted from our previous study [18] (Additional files 1, 2, 3 and 4). The main content of the questionnaire includes patient demographic characteristics (e.g., sex, age, education, residential area, and medical insurance status), illness duration, symptoms, severity rating, diagnosis, antibiotics, and other medicines prescribed. EPI DATA 3.1 will be used to create a data entry interface for all the on-site and telephone follow-up interviews. Table 3 summarizes measure by measure time schedule for data collection.

**Table 3 Tab3:** SPIRIT schedule of outcome measures

**Category**	**Outcome measure**	**Initial consultation**	**Days after consultation**				
			**7**	**14**	**21**	**180**	**365**
Primary measure	Number of days with antibiotics use	√	√	√	√		
Secondary measures	Illness duration	√	√	√	√		
	Illness severity	√	√	√	√		
	Times of re-visits				√		
	Antibiotics re-prescription				√		
	Knowledge about and attitude toward antibiotics					√	√
	Times of re-occurrence of RTIs					√	√
	Health service seeking for re-occurred infections					√	√
	Antibiotics consumption for re-occurred infections					√	√
	Quality of life (EQ-5D-5L)	√	√	√	√		
	Attitude toward intervention messages		√	√			
	Understanding of intervention messages		√	√			

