#### Data analysis

The data collected will be used to compare the differences between the control and intervention groups as a whole and between subgroups in the intervention arm in terms of days of antibiotic use per episode of RTIs; times of re-visits to clinics and antibiotics re-prescription for the same RTI; quality of life; times of re-occurrence of RTIs and related health service seeking and antibiotics consumption for re-occurred infections; and scores of patients’ knowledge about and attitude toward antibiotics.

Estimation of statistical significance and confidence intervals will assume a type I error established in alpha=0.05, using the IBM SPSS V25 statistics package. Missing data will be treated as missing at random and imputed using a chained-equations multiple imputation model. Initial data analysis will consist of descriptive summaries intended to examine the patterns of the various measurements and check for normality of the continuous variables. And necessary transformations will be explored and selected, if necessary, to induce approximate normality. Regarding the numerical variables between two groups, *t*-test of independent samples for mean comparisons will be carried out. The chi-square test will be conducted for categorical variables (non-continuous). Lastly, no interim analysis is planned.

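### Illness duration is right-censored at day 21, but the protocol has no rule for patients still ill then, and its general t-test and missing-at-random rules can attenuate a real lengthening of illness

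*Protocol article*

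**What the plan says.** Table 2 of the protocol article defines illness duration, a secondary outcome, as "Days from the initial consultation to the day when the patient has reported full recovery". It draws on one questionnaire item in each of Additional files 1 to 3.

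Under Data collection, "the follow-up interviews are scheduled at 7, 14, 21,180, and 365 days after the baseline". Table 3 marks illness duration and severity at the initial consultation and days 7, 14 and 21, but not at days 180 or 365.

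The Data analysis section gives general rules only:
- Numerical variables are compared between two groups by t-test ("test of independent samples for mean comparisons will be carried out").
- Where normality is doubtful, "necessary transformations will be explored and selected, if necessary, to induce approximate normality".
- "Missing data will be treated as missing at random and imputed using a chained-equations multiple imputation model".

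It names no censoring rule, time-to-event method or restricted mean. Its list of comparisons covers antibiotic days, re-visits, re-prescription, quality of life, recurrence and its consequences, and knowledge and attitude. Illness duration and severity are not in that list, although Outcome measures and Table 2 name both as secondary outcomes.

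**The concern.** A patient who has not recovered by the day-21 interview has a duration known to be longer than 21 days, but the definition assigns no number. That is right-censoring. If such a patient is handled as an ordinary missing value, the reason for missingness is the length of the illness itself, so missing at random is not credible without strong proxies. The imputation model would also have no observed duration above 21 days from which to learn the tail.

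The messages tell patients to "avoid antibiotics use whenever possible". Duration and severity are therefore the outcomes that most directly show whether patients in the message arm fare worse. An analysis that under-represents slow recoverers pulls the duration comparison towards no difference when the messages do prolong illness. Leaving both outcomes off the list of comparisons adds to the uncertainty about how they will be reported.

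**Working it through.** **The plan's own figures.** The article gives no figure for illness duration. Its sample size for antibiotic days does reproduce: 2 × (1.96 + 1.2816)² × 2.06² / 0.87² = 117.8, so 118 per arm; 2.45 × 118 × 2 × 1.2 × 1.2 = 832.6, so 833; 833/24 is about 35 per centre. This point does not affect it.

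**Inputs.** From the article: observation to day 21, and the design effect of 2.45. Assumed, because the article gives none: the distribution of recovery times and the lengthening in the message arm.

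**Quantities compared**, with T the recovery time and p = P(T > 21):
- full difference: difference in mean T;
- restricted difference: difference in mean of min(T, 21), with unrecovered patients counted at 21;
- recovered-only difference: difference in mean of T given T ≤ 21. This approximates missing-at-random imputation that carries little information on the tail.

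**Exponential illustration**, means 10 and 12 days:
- p = exp(−21/10) = 0.122 and exp(−21/12) = 0.174.
- Recovered-only mean = μ − 21p/(1 − p) = 7.07 and 7.58; difference 0.51.
- Restricted mean = μ(1 − p) = 8.78 and 9.91; difference 1.14 (before rounding).
- Kept: 0.51/1.14 = 45%.

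**Lognormal range.** Control median 7, 10 or 14 days, log-SD 0.5 or 0.7, message-arm times 15% or 30% longer, with 2 million simulated draws per scenario. Selected results:

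| Median, log-SD, lengthening | Unrecovered at day 21, control v message | Full difference (days) | Restricted to day 21 | Recovered-only | Recovered-only / restricted |
|---|---|---|---|---|---|
| 7, 0.5, 15% | 1.4% v 2.8% | 1.19 | 1.12 | 0.96 | 86% |
| 10, 0.5, 30% | 6.9% v 16.9% | 3.40 | 2.58 | 1.81 | 70% |
| 10, 0.7, 30% | 14.5% v 24.7% | 3.84 | 2.17 | 1.32 | 61% |
| 14, 0.7, 30% | 28.2% v 41.9% | 5.37 | 2.02 | 1.17 | 58% |

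Across all twelve scenarios the recovered-only difference keeps 58% to 86% of the restricted difference and 22% to 81% of the full difference. The restricted difference itself keeps 38% to 94% of the full difference, since nothing is seen after day 21, but it keeps every unrecovered patient in the comparison.

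**Power.** Take 833/1.44/2 = 289 analysed per arm and divide by 2.45, assuming that the design effect for antibiotic days carries over to duration. In the third row power is 0.79 for the restricted comparison and 0.48 for recovered-only. In the second row it is 0.98 and 0.87.

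**Limiting case.** Suppose the arms differ only in the share unrecovered, 5% v 15%, with a recovered mean of 8 to 10 days in both. Scoring at 21 gives (0.15 − 0.05) × (21 − 8) = 1.3 days or (0.15 − 0.05) × (21 − 10) = 1.1 days. Recovered-only gives 0.

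**The case against.** The strongest reply is that no sentence says unrecovered patients are treated as missing. That reading joins a definition to two general rules. A patient interviewed at day 21 and recorded as still ill has an observed status, and scoring that patient at 21 days fits the text equally well. The questionnaire items behind the definition are in additional files not shown here and may settle the coding, and a separate analysis plan may set a censoring rule. This stands: a reader might infer that the plan imputes these patients as missing at random and so hides harm, but the document does not establish that.

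The t-test is not wrong in itself. With complete follow-up to day 21, restricted mean time to recovery is the mean of durations capped at 21, so a comparison of means can target the right quantity. The difficulty is the scoring of unrecovered patients; the allowance for clustering is a separate matter.

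A reader might also infer that many patients will be unrecovered. The document does not support this. Its worked example for a common cold tells the patient not to return "unless you do not get better within 14 days", but that is a threshold for seeing a doctor and lies inside the 21-day window. The Text messages package section says that most common symptoms are gone in roughly a week. Acute bronchitis and COPD exacerbation are eligible, but no case mix is given.

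Finally, severity at days 7, 14 and 21 could enter the imputation model and recover part of the loss. Severity, EQ-5D-5L, re-visits and actively sought adverse events are other places where harm could appear.

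What the reply does not remove is that the article commits to a test and a missing-data rule without saying how they apply to an outcome that its own definition and schedule leave censored.

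**Conclusion.** The point holds in a limited form. Illness duration is right-censored at day 21, the article does not say what value an unrecovered patient receives, and its general missing-data rule does not suit values that are absent because the patient is still ill. Following the text in that way can attenuate a real lengthening of illness in the message arm. It cannot be said that the plan will do so, or that harm would be hidden.

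The size depends wholly on assumed recovery times. The recovered-only figures approximate an imputation that knows little about the tail, so they lean towards the larger loss. A reader might conclude from the exponential illustration that more than half the difference generally disappears, but that is one scenario and falls outside the lognormal range. If the messages do not lengthen illness, there is no difference to attenuate.

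The absence of duration and severity from the listed comparisons is a plain inconsistency that needs no assumption. As this is a secondary outcome but a direct check on harm, the correction should be made; the primary analysis and the sample size are untouched.

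**What to change.** In the Data analysis section or the analysis plan:

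1. State that patients not fully recovered are censored at day 21, or at last contact if earlier, and are not treated as missing.
2. Compare restricted mean time to recovery to day 21 between arms (with complete follow-up, the mean of durations capped at 21), or use a time-to-recovery model. Allow for clustering by centre and for the county strata used in the allocation.
3. Report the proportion unrecovered at day 21 by arm.
4. Add illness duration and severity to the listed between-arm comparisons.

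The cost is analysis wording and a little extra analysis. The scheduled interviews already ask about recovery, so no new contact is needed, and the sample size does not change.

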According to our previous studies and others, patients in China have various beliefs and habits that lead to excessive use antibiotics. They lack a general understanding of uses, especially resistance and other side effects, of antibiotics [21]. Some of them believe that antibiotics help in treating almost all diseases. Although China policy requests that (since 2020) all antimicrobials must be dispensed with a prescription in all retail pharmacies [22, 23], it is not fully enacted in rural areas [24, 25]. As a result, patients can easily get antibiotics from retail pharmacies without prescriptions. In addition, most consultations in China are very short and doctors seldom have time or desire to discuss antibiotics with their patients, while patients on the other hand seldom have the opportunity to explicitly express their expectations about antibiotics. These all point to a clear need for patient education. This study is an innovative attempt in this regard.

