Day 4	Dear [PatientName], [DiseaseDiagnosis] is easy to transmit to family members and friends. Please avoid contact with them, especially children and the elderly in the local community for 1-2 weeks. Please practice ventilating your living rooms, wearing masks when you go out or meet with people, avoiding eating out and going to crowded places. From [DoctorName] with [ClinicName].
Day 5	Dear [PatientName], most respiratory tract infections such as [DiseaseDiagnosis] are caused by virus. Generally, they are self-limiting without oral medicines or injections. Antibiotics do not work for viral infections, which can neither ease the severity of symptoms nor shorten the duration. Most importantly, antibiotics can cause antibiotic resistance and various other side effects. From [DoctorName] with [ClinicName].
Day 6	Dear [PatientName], taking antibiotics (such as amoxicillin and cephalosporin) will weaken your own body immunity, and will kill the good bacteria in your gut as well, or upset the balance of/in your stomach. The more antibiotics you take, the higher chance that you suffer from an antibiotic-resistant-infections. This infection is not only serious, but also difficult to treat and are easy to transmit to family members. From [DoctorName] with [ClinicName].
Day 7	Dear [PatientName], when you feel unwell with respiratory tract, you should not go to retail pharmacies to buy antibiotic. China National Medicine Administration Bureau has banned pharmacies to sell antibiotics to residents without a doctor's prescription. China National Health Commission advises not to have a drip or take antibiotics for coughs, cold, sore throat or earache. From [DoctorName] with [ClinicName].
Day 8	Dear [PatientName], are you feeling any better from your [DiseaseDiagnosis]? If yes, you seem to be recovering as expected; If not, you should better see your doctor again. As antibiotics do almost no good for respiratory tract infections but have many side effects, we recommend you clearly tell your doctor that you don't want antibiotics whenever you consult a doctor in the future; or, if you are prescribed with antibiotics, ask your doctor whether the antibiotics can be avoided. From [DoctorName] with [ClinicName].

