### Trial evaluation

#### Outcome measures

The primary outcome is the number of days of antibiotics use, including antibiotics obtained before and after the initial consultation. The secondary outcomes include (1). illness duration and severity, (2) patients’ attitude and understanding of intervention messages, (3) patients’ quality of life, (4) re-visits and antibiotic usage, (5) patients’ knowledge and attitude toward antibiotics, and (6) recurrence of RTIs and related health service and antibiotics use. Definition and calculation of these measures are summarized in Table 2.

**Table 2 Tab2:** Primary and secondary measures for trial evaluation

Measure	Definition/calculation

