**Primary measure**	
-Number of days with antibiotics use	Days of antibiotics use from onset of the RTI to the initial consultation + days of antibiotics use from day 1 to 21 after the initial consultation based on the patient’s responses to question item A5d in Additional file 1, B2 in Additional file 2, and item C2-C4 in Additional file 3. Here, days of antibiotics use is defined as days on which the patient has used any antibiotics.

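### Antibiotic consumption in recurrent infections is defined in Table 2 as a count of prescriptions, so as written it does not measure use

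*Protocol article*

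**What the plan says.** The outcome list (Outcome measures) includes "recurrence of RTIs and related health service and antibiotics use". In Table 2 the antibiotic part of this becomes a row named "Antibiotics consumption for re-occurred infections". Its definition reads "Times of antibiotics prescriptions for re-occurring RTI episodes 180 days or 365 days following the initial consultation", taken from patients' answers to items D2b3, D2c3 and D3c3 of Additional file 4. The abstract and the Data analysis section also call the outcome consumption.

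The Background says that in rural areas "patients can easily get antibiotics from retail pharmacies without prescriptions". Two messages in Table 1 address this supply. Day 7 tells patients "you should not go to retail pharmacies to buy antibiotic". Day 11, which is about the next illness, says "do not go to retail medicine shop to buy antibiotics without a prescription, and do not take leftover antibiotics", and also "please do not hurry seeing a doctor but wait and watch its progression".

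The primary outcome in Table 2 follows a different rule: it counts "days on which the patient has used any antibiotics", up to day 21.

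**The concern.** The name promises antibiotics taken, while the rule counts antibiotics prescribed. The two can part in both directions. Purchased or leftover antibiotics are taken without being prescribed. A prescribed course may also go unused, and the Text messages package section describes Day 3 as asking patients to delay or forgo antibiotics that have already been prescribed.

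The gap lies where the intervention acts. Day 7 and Day 11 aim at non-prescribed supply, which a prescription count does not see. Day 11 also discourages early consulting, and fewer visits bring fewer prescriptions whatever patients take from elsewhere.

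At stake is the trial's statement on longer-term use. In Tables 2 and 3 the only measures at 180 and 365 days are knowledge and attitude, number of recurrences, clinic visits for recurrences, and this one. No other measure at those times speaks to antibiotic intake.

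**Working it through.** The plan gives no figure for this outcome, so there is none to reproduce. The sample size rests on the primary outcome and is not touched.

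**Reading the texts side by side**

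- Name (Table 2) and outcome list: consumption, use.
- Written rule (Table 2): number of prescriptions.
- Another row of Table 2 is named for re-prescription, so the plan has separate names for prescribing and consuming.
- Setting (Background): pharmacy supply without a prescription is easy.
- Behaviour targeted for future episodes (Table 1, Day 11): pharmacy purchase, leftovers and early consulting.

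The mismatch is therefore between the label and the definition within one row, and it matters because of the setting and the messages.

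**Illustration of what the written rule can and cannot show**

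All inputs here are assumed; the documents give none of them. Per 100 recurrent episodes in the control arm, take 60 prescribed and 20 non-prescribed courses, all taken: 80 in total.

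| Assumed change in the intervention arm | Prescriptions | Courses taken | Measured fall | True fall |
|---|---|---|---|---|
| 20% fewer prescriptions, not replaced | 48 | 48 + 20 = 68 | 12/60 = 20% | 12/80 = 15% |
| 20% of prescribed courses replaced one for one by pharmacy or leftover courses | 48 | 48 + 32 = 80 | 20% | 0% |
| Non-prescribed use halved, prescriptions unchanged | 60 | 60 + 10 = 70 | 0% | 10/80 = 12.5% |
| 20% of prescribed courses not taken | 60 | 48 + 20 = 68 | 0% | 12/80 = 15% |

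With replacement of 10% or 30% instead of 20%, prescriptions go to 54 or 42, a measured fall of 10% or 30%, and courses taken stay at 80.

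The third row in general form: if non-prescribed courses are a share s of all courses and are halved, the true fall is 0.5 × s and the measured fall is 0. For an assumed s of 20% to 50% the true fall is 10% to 25%.

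The second row needs one-for-one replacement of courses. If clinic-treated episodes move instead, the result differs. Take 100 such episodes with antibiotics prescribed in 80% (borrowed from the Background's estimate of over 80% for RTI patients), and let 20 move to pharmacy antibiotics. Prescriptions go from 80 to 0.8 × 80 = 64, a measured fall of 20%. Courses taken go from 80 to 64 + 20 = 84, a rise of 4/80 = 5%.

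So a measured fall of 20% fits a true fall of 15%, no change, or a rise of 5%, and no measured change fits a true fall. This shows that the measure is ambiguous. It does not estimate a bias in this trial.

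**The case against.** The strongest reply is that the definition does not end with the word prescriptions. It says that the outcome is computed from three questionnaire items, and these may cover pharmacy or leftover antibiotics. The day-21 rows give a hint: item C4a3 counts towards re-prescription, yet no C4a item counts towards re-visits, so the authors may use prescription loosely for several routes of supply. A reader might infer that the trial collects nothing on non-prescribed use in recurrences. The documents do not support that, because Additional file 4 is not shown. This part of the reply stands. What remains is that the written rule and the label disagree, and that an analyst who follows the rule would count prescriptions.

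A reader might also infer that the secondary outcome must use the same rule as the primary. It need not: the two cover different episodes, windows and units. The primary outcome's rule only shows that counting any antibiotic is workable in this trial.

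Third, the visit-driven mechanism can be examined in part, since recurrences and clinic visits for them are also recorded; visits per recurrence and prescriptions per visit can be reported. Fewer visits are also what Day 11 intends, and Day 8 asks patients to decline antibiotics at future consultations, so prescriptions are worth reporting in their own right. This stands too, but neither ratio shows what was taken outside the clinic or left untaken.

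Last, a move to pharmacies would run against the messages themselves, and nothing in the documents shows that it will happen. That is correct, and it is why no false benefit is claimed here.

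**Conclusion.** The point holds in a limited form. As written, the outcome counts prescriptions while it is named and listed as consumption or use. It omits antibiotics obtained without a prescription or left over, counts prescribed courses that are not taken, and cannot by itself separate less use from fewer consultations or a change of source.

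Whether the needed data are missing is open and turns on the three items in Additional file 4. If those items record other sources, only the wording of Table 2 is at fault. The size and direction of any bias are unknown; every percentage in the illustration rests on assumed shares and shifts. The outcome is secondary and does not drive the sample size, and the primary outcome already covers any antibiotic to day 21. This should be corrected, but it does not threaten the main result.

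**What to change.** Define the outcome as the number of recurrent RTI episodes in which any antibiotic was taken, in total and by source (prescribed, bought without a prescription, left over). Report prescriptions as a separate component. Counting episodes rather than days keeps the recall task modest over 180 or 365 days.

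Then reconcile the definition with items D2b3, D2c3 and D3c3. Only if they do not ask about source and intake, add one source question to the 180- and 365-day calls that are already scheduled, in both arms alike.

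If the source data cannot be collected, rename the outcome as antibiotic prescriptions for recurrent infections in Table 2, the outcome list and the analysis section, and draw no conclusion on consumption from it.

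The cost is a small change of wording through the amendment route that the article describes, and possibly one extra recall question. Because recruitment opened on 1/12/2022, patients whose calls are already past would lack an added question, so the number of patients asked should be reported by arm.
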